## Abstract

**Background:**

Over the last 30 years the number of people who drink alcohol at harmful levels has increased in many countries. There have also been large increases in rates of sexually transmitted infections. Available evidence suggests that excessive alcohol consumption and poor sexual health may be linked. The prevalence of harmful alcohol use is higher among people attending sexual health clinics than in the general population, and a third of those attending clinics state that alcohol use affects whether they have unprotected sex. Previous research has demonstrated that brief intervention for alcohol misuse in other medical settings can lead to behavioral change, but the clinical- and cost-effectiveness of this intervention on sexual behavior have not been examined.

**Methods:**

We will conduct a two parallel-arm, randomized trial. A consecutive sample of people attending three sexual health clinics in London and willing to participate in the study will be screened for excessive alcohol consumption. Participants identified as drinking excessively will then be allocated to either active treatment (Brief Advice and referral for Brief Intervention) or control treatment (a leaflet on healthy living). Randomization will be via an independent and remote telephone randomization service and will be stratified by study clinic. Brief Advice will comprise feedback on the possible health consequences of excessive alcohol consumption, written information about alcohol and the offer of an appointment for further assessment and Brief Intervention. Follow-up data on alcohol use, sexual behavior, health related quality of life and service use will be collected by a researcher masked to allocation status six months later. The primary outcome for the study is mean weekly alcohol consumption during the previous three months, and the main secondary outcome is the proportion of participants who report unprotected sex during this period.

**Discussion:**

Opportunistic intervention for excessive alcohol use has been shown to be effective in a range of medical settings. The SHEAR study will examine whether delivering such interventions in sexual health clinics results in reductions in alcohol consumption and will explore whether this is associated with changes in sexual behavior.

## Background

Concerns have been raised regarding increased levels of alcohol consumption in many countries [1]. It is estimated that as many as one in five adults drink too much alcohol in the UK [2]. This may take the form of sustained excessive consumption or episodic bouts of ‘binge’ drinking. Excessive alcohol consumption can lead to a range of physical and mental health problems, which result in increased use of healthcare services and costs to society associated with sickness absence, unemployment, accidents and crime [3].

The proportion of people who drink excessively has increased considerably over the last 30 years, especially among people aged under 25 [4]. Increasing levels of alcohol misuse have been accompanied by large increases in rates of sexually transmitted infections [5]. The figures published by the Health Protection Agency (HPA) in 2010 showed a record level of nearly half a million new diagnoses. While we do not know if alcohol use is implicated in this increase, epidemiological data suggest that it may be. For instance, cross-sectional data from a sample of over 1,000 young people in nine European cities demonstrated that alcohol consumption was associated with the number of sexual partners and age at first sexual contact [6]. In the United States, changes in the price of alcohol in the 1980s and 1990s were highly correlated with changes in rates of gonorrhoea [7]. Policies which succeeded in reducing drunk driving rates in young men in the United States were associated with subsequent reductions in gonorrhoea rates among young males [8]. Further evidence to support an association between alcohol consumption and sexual behavior comes from cross-sectional surveys, which have also demonstrated high levels of alcohol consumption among people attending sexual health clinics [9-11]. In one study, over a third of participants indicated that their attendance was alcohol related [10].

Systematic reviews of brief interventions for alcohol misuse have shown that they lead to clinically important reductions in alcohol consumption across a range of healthcare settings [12,13]. Interventions delivered in a single session appear to be as effective as more lengthy ones [14]. Stepped interventions in which people receive interventions of greater intensity depending on the extent of their needs have also demonstrated positive effects [15,16].

To date, there has been only one randomized trial of brief intervention for alcohol misuse in a sexual health setting [17]. In this study, half of a total sample of 184 people found to be drinking excessively was offered a brief intervention delivered by one of two trained nurses. At a three-month follow-up 62 % of those that received the brief intervention reported consuming less alcohol compared to 47 % of those in the control arm of the trial. While this study demonstrated the feasibility of a randomized trial of brief alcohol intervention for people attending sexual health clinics, the intervention was delivered by a research nurse, rather than those already working in the clinic, limiting the generalizability of the study findings. In addition, the impact of brief intervention on sexual health outcomes was not explored and the costs and cost-effectiveness of the intervention were not examined. There is widespread recognition of the need for experimental studies to examine the clinical effects and cost-effectiveness of screening and brief intervention for alcohol misuse for people who attend sexual health clinics [18].

### Research objectives

The aim of the SHEAR study (Sexual Health and Excessive Alcohol: Randomized trial) is to examine the effectiveness and cost-effectiveness of opportunistic brief intervention for alcohol misuse for people who attend sexual health clinics and consume excessive alcohol. To achieve this aim we will:

1. Test whether brief intervention reduces subsequent alcohol consumption measured six months later compared to the control treatment.

2. Examine whether brief intervention compared to control treatment is associated with changes in sexual behavior.

3. Examine the cost-effectiveness of brief intervention compared to control treatment.

#### Hypotheses

i. Brief intervention for those attending sexual health clinics and drinking excessively reduces mean weekly alcohol consumption over a 12-week period prior to the 6-month follow-up interview (that is, weeks 13 to 24 after intervention).

ii. Brief intervention for those attending sexual health clinics and drinking excessively reduces the likelihood of unprotected sexual intercourse over a 12-week period prior to the 6-month follow-up interview.

iii. Brief intervention for those attending sexual health clinics and drinking excessively is more cost-effective than control treatment.

## Methods/Design

The design is a two parallel-arm, single-blind, individually randomized controlled trial. The trial will be an integrated clinical and economic evaluation and will compare the intervention versus control treatment on alcohol consumption, sexual behavior, health-related quality of life and costs in the six months following randomization. We will also conduct a parallel process evaluation, which will include an examination of the uptake of study interventions and an analysis of qualitative data from in-depth interviews with a sample of service users and providers. These data will help us to examine the uptake and acceptability of the interventions being used and explore the relationship between the study context and outcomes.

### Study setting

Study participants will be recruited from three sexual health clinics in London. Collectively, these clinics serve a diverse population with high levels of alcohol misuse and poor sexual health [19,20].

### Recruitment

At each clinic where we recruit participants, information about the study will be displayed on posters in waiting rooms. On days when recruitment is taking place, clinic staff will hand all those attending the service a postcard with information about the study and ask people if they would be willing to meet a researcher. If they agree to this, a researcher will explain the rationale for the study and give them a copy of the Patient Information Leaflet. The Patient Information Leaflet states that we are conducting a study about ‘sexual health and lifestyle advice’ and only refers to alcohol in the context of other aspects of lifestyle, such as exercise, diet and smoking. The researcher will encourage potential participants to spend as much time as they want asking questions about the study and considering whether they wish to take part or not. Before any trial specific procedures are performed, the patient will sign and date the Informed Consent Form. For those willing to provide consent, eligibility to participate in the study will be assessed and baseline clinical and demographic data will be collected. Potential participants will be asked five questions on ‘health and lifestyle’. We will check with participants the contact details they have given to clinic staff to make sure they are correct. We will ask participants for other information that may assist follow-up and seek written informed consent to contact their general practitioner solely for the purpose of helping us collect follow-up data. A recruitment flow chart is presented in Figure 1.

**Figure 1 F1:**
[figure not shown]
Recruitment flow diagram.

### Randomization

Those who are eligible will be randomized to brief intervention or control treatment. The researcher will provide those who are ineligible with written information about health and lifestyle. Remote telephone randomization will be undertaken through a fully automated telephone-based service operated by an independent Clinical Trials Unit. Equal numbers of participants will be randomized to each arm of the trial. We will use permuted blocks stratified by the clinic, with block size randomly assigned to between four and six. The researcher will notify the treating clinician concerning which arm of the trial they are in. This researcher will play no part in the collection of follow-up data.

### Follow-up

Three months after randomization, study participants will receive a phone call, text message or an email thanking them for taking part in the study, reminding them that they will be contacted in three months’ time to complete the follow-up interview, and asking them to let us know whether their contact details are likely to change during this period. If, at six months, our attempts to contact a participant are unsuccessful, we will check their contact details against those given during any subsequent visits to the clinic. If the participant provided consent for us to contact their general practitioner, a family member or friend we will contact them to obtain updated contact details for the participant. Follow-up interviews will be carried out by telephone, unless the participant requests a face-to-face interview. Any face-to-face interview will take place at the clinic at a time which is convenient for the participant. Any travel costs or other reasonable expenses incurred by the participant will be reimbursed. All participants will be offered a £15 honoraria after completion of the six-month follow-up interview.

### Planned interventions

We will test the effects of Brief Advice and referral delivered by the treating clinician. The intervention is based on that used in a previous trial conducted in an emergency medical setting [15]. The intervention consists of:

· Confirming the current level of alcohol use and brief feedback that alcohol use at that level has the potential to harm health

· Making a link between alcohol and clinic attendance

· Written information on alcohol and health in the form of a leaflet recommended by the Department of Health: *‘How much is too much’*[21]

· The offer of an appointment with an Alcohol Health Worker (AHW).

This form of intervention was previously tested in a feasibility study in a sexual health clinic and found to be acceptable to clinicians working in this busy clinical setting [9].

On days when participants are recruited from the clinics, an Alcohol Health Worker will be available to see those who are willing to receive further help. Brief Intervention delivered by the AHW will last up to 30 minutes and use the ‘FRAMES’ approach [14,22]. For any participant who is drinking at a harmful or dependent level, the AHW will have the option of arranging a follow-up appointment or referring them on to local alcohol services for individual alcohol counseling, detoxification and so on. In the event that the participant is unable to attend an appointment that day they will be offered an appointment on a later date or telephone-based support and advice.

#### Control treatment

Those randomized to control treatment will be offered a copy of the leaflet *‘Five Choices to Help You Stay Healthy’*[23], which provides general information on preventative health, including alcohol use, diet, exercise, cigarette smoking and details of how to obtain further information about health and lifestyle.

### Treatment integrity

Treatment integrity will be maximized through training, supervision and checks on written notes kept by clinicians and Alcohol Health Workers. All clinicians who deliver the brief intervention will receive training in accordance with Department of Health guidelines (http://www.alcohollearningcentre.org.uk). All Alcohol Health Workers who take part in the study will be experienced practitioners who have undertaken specific training in counseling people who misuse alcohol. All Alcohol Health Workers will receive regular clinical supervision. Clinical supervisors will encourage Alcohol Health Workers to discuss work with trial participants along with other patients they see.

Front-line clinicians will be asked to complete a short tick box proforma for each study participant to indicate whether the four components of the Brief Advice and referral are delivered. Alcohol Health Workers will be asked to complete a longer proforma which will record the number and length of session(s), interventions delivered during the session(s) and further information on referrals that were subsequently made. The proforma is based on that used to assess treatment fidelity in our previous trial of brief intervention in the Accident and Emergency Department [15]. At the end of the study, we will inspect a random sample of 20% of all study proforma to identify the proportion of people in the experimental arm of the trial who receive the interventions they were allocated.

### Planned inclusion/exclusion criteria

To maximize generalizability of study findings, we have kept our inclusion criteria broad and limited our exclusion criteria. To participate in the study people must be aged 19 years or above, be drinking excessively according to the Modified-Single Alcohol Screening Question [24] and be willing to provide written informed consent to take part in the study. The age limit is because people younger than 19 years attending sexual health clinics receive health advice. We will exclude any person who is unable to communicate in English sufficiently to complete baseline questionnaires, anyone who does not have an address or contact telephone number, and anyone who believes they may not be contactable in six months’ time.

### Measures

#### Baseline measures

Basic demographic data on age, gender, and ethnicity will be extracted from clinic records and checked with the patients to make sure they are correct.

All patients consenting to take part will be asked to complete a computer-assisted self-completion interview [25,26].

Alcohol consumption will be assessed using the Modified-Single Alcohol Screening Question (M-SASQ). The M-SASQ is a brief validated measure of harmful alcohol use that is acceptable to patients in general medical settings [24]. It consists of a single question - for men: ‘How often do you drink more than eight units of alcohol on one occasion?’ and for women: ‘How often do you drink more than six units of alcohol on one occasion?’ To help people answer this question they are shown a card which describes what a unit of alcohol is. Those drinking at such levels once a month or more are considered eligible. The question on alcohol is embedded in a series of four other questions asking about diet, exercise and smoking.

In addition, eligible patients will be prompted to answer questions on their sexual behavior and health-related quality of life (EuroQol 5 Dimensions (EQ-5D) [27]).

### Follow-up measures

Follow-up data will be obtained by a telephone interview by a researcher who is masked to the participant’s allocation status.

Alcohol consumption data in the last 90 days will be collected using the Form 90. The Form 90 is a validated alcohol consumption assessment tool which provides a detailed day-by-day account of alcohol use in the 90 days prior to the interview [28].

In addition, participants will be asked about hazardous drinking (Alcohol Use Disorders Identification Test-Consumption (AUDIT-C) [29]), sexual behavior in the last three months, health-related quality of life (EQ-5D [27]) and resource use during the previous six months (Adult Service Use Schedule [30]).

### Outcomes

1. Primary: Mean weekly units of alcohol consumed during the previous 90 days using the Form 90 [28].

2. Main secondary: Whether or not the participant has had unprotected sex in the last three months.

3. Other secondary: Mean units consumed per drinking day and percentage days abstinent, both measured using the Form 90, and whether or not the participant is drinking alcohol at hazardous levels using the AUDIT-C [29].

Our secondary sexual behavior outcomes are based on those used in a previously reported study [31] and will comprise: total number of sexual partners during the last three months, any incidence of regretted sex in the last three months, number of people they had unprotected sex with (anal or vaginal sex without a condom) in the three months before the interview, any incidence of unprotected sex while drunk in the last three months, how long they knew their last sexual partner before they had sex with them, unwanted pregnancy and any new diagnosis of a sexually transmitted infection in the last three months.

### Sample size

Initial sample size calculations were based on comparison of the primary outcome. In order to achieve 80% power to detect a mean weekly difference of 23.4 units of alcohol consumption with standard deviation of 58 units [15], 97 evaluable participants per arm were needed. An inflation factor of 1.15 for clustering by clinician in the intervention arm was considered [32], based on an intracluster correlation coefficient of 0.04 [33] and a cluster size of 7 in the intervention arm. Together with an anticipated 30 % drop-out rate at six months, the initial recruitment target was, therefore, 160 per arm.The first months of the trial showed that recruitment and retention rates were higher than expected; the sample size was, therefore, modified to provide additional power to test both the primary and main secondary hypotheses (a reduction in unprotected sexual intercourse) of interest.

The final sample size was based on a practical size of 380 per arm (760 in total). If 65% of participants had unprotected sex in the control group compared to 50% in the intervention arm, the power to detect such an effect would be above 90%, assuming a 25% drop out, and a clustering design effect of 1.15. The power would remain above 80% if the absolute difference is 13%.

### Statistical analysis

Baseline characteristics will be reported by treatment arm. The primary outcome will be analyzed using random-effects linear regression adjusted for age, sex and harmful alcohol use measured at baseline, testing for the presence of an intervention effect between the two arms. The random-effects model will take into account clustering by sexual health clinic and, in the intervention arm, by treating clinician [34].

Alcohol consumption is not expected to be normally distributed and particular care will be taken to check the validity of the regression, including normality and homoscedasticity of the residuals. If the assumptions are violated, sensitivity analysis will be performed as appropriate.

Participants who dropped out from the trial will be compared to the completers. Sensitivity of the results to missing data will be assessed by performing multiple imputations; further models allowing for missing not at random mechanism will also be considered [35].

The main secondary outcome will be compared in the same way as the primary, using logistic regression and adjusting for unprotected sex at baseline. Other secondary outcomes will be compared using linear or logistic regression, and adjusted for baseline value, as appropriate.

In order to assess for possible heterogeneity of the intervention effect, primary and main secondary outcomes will also be reported by the following subgroups: gender, age (<25, 25 to 35, 35 and older), ethnicity (white vs. other), sexual orientation (heterosexual vs. other). All analyses will be performed according to the randomization arm (intention-to-treat), and two-sided *P*-values considered significant when below 0.05.

The economic evaluation will take the NHS/Personal Social Services perspective preferred by the National Institute for Health and Clinical Excellence [36] and shown to be the key cost sectors in our previous research of brief intervention for alcohol misuse [30]. Data on uptake of the brief intervention will be collected from records to avoid patients revealing their treatment group to the research assessors. Data on indirect time, including preparation and supervision, will be collected directly from the treating clinician. Data on the use of other health and social services will be collected using the Adult Service Use Schedule (AD-SUS) adapted for alcohol misuse in previous research [30]. The cost of the brief intervention will be directly calculated from salaries using a micro-costing approach [37]. National UK unit costs will be applied to medication, hospital contacts and community health and social services [38,39].

Differences in mean costs will be analyzed using standard parametric t-tests with the validity of results confirmed using bias-corrected, nonparametric bootstrapping (repeat re-sampling) [40]. Despite the skewed nature of cost data, this approach is recommended to enable inferences to be made about the arithmetic mean [41]. Cost-effectiveness will be assessed through the calculation of incremental cost-effectiveness ratios [42] and will be explored in terms of alcohol consumption (primary economic analysis) and quality adjusted life years (QALYs) using the EQ-5D measure of health-related quality of life (secondary economic analysis). Uncertainty around the cost and effectiveness estimates will be represented by cost-effectiveness acceptability curves [43].

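### The model stated for the other secondary outcomes omits the clinician, clinic and covariate terms of the primary model, and three alcohol outcomes have no baseline value to adjust for

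*Protocol article*

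**What the plan says.** The Statistical analysis section of the protocol article describes three tiers.

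- **Primary outcome.** "The primary outcome will be analyzed using random-effects linear regression adjusted for age, sex and harmful alcohol use measured at baseline". On clustering: "The random-effects model will take into account clustering by sexual health clinic and, in the intervention arm, by treating clinician".
- **Main secondary outcome.** "The main secondary outcome will be compared in the same way as the primary, using logistic regression and adjusting for unprotected sex at baseline".
- **Remaining tier.** "Other secondary outcomes will be compared using linear or logistic regression, and adjusted for baseline value, as appropriate".

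The Outcomes section places three alcohol measures in the last tier: "Mean units consumed per drinking day and percentage days abstinent, both measured using the Form 90", together with hazardous drinking on the AUDIT-C. The secondary sexual-behavior outcomes are in the same tier.

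The Baseline measures section gives the M-SASQ as the only alcohol measure at entry, alongside sexual behavior and the EQ-5D. The Form 90 and AUDIT-C appear only under Follow-up measures. The Discussion indicates that the short baseline alcohol assessment is deliberate, because questioning people about drinking may itself change it. On allocation, the Randomization section says: "We will use permuted blocks stratified by the clinic, with block size randomly assigned to between four and six".

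**The concern.** The statement that an outcome is handled like the primary is made for the main secondary only. The sentence on the remaining outcomes names a type of regression and a baseline term, and nothing else. For the three alcohol outcomes that baseline term does not exist. An analyst following the text would therefore fit a model with treatment arm alone, although age, sex, M-SASQ answer, clinic and treating clinician are all available.

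The plan treats clinician clustering in the intervention arm as real: it inflates the sample size for it and models it for the primary outcome. That clustering comes from who delivers the advice, so it should not be assumed away for companion outcomes from the same follow-up interview. These outcomes are judged at the same two-sided 0.05 level. Two of them come from the same Form 90 as the primary outcome, so a difference in model also makes the alcohol results harder to read together.

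**Working it through.** **Inputs.** From Sample size: difference 23.4 units, SD 58, 80% power, ICC 0.04, cluster size 7 in the intervention arm, inflation factor 1.15, dropout 30% (initial) and 25% (final), 380 per arm. From Discussion: over 30 clinicians. From Statistical analysis: two-sided 0.05.

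**1. The plan's own figures reproduce.**
- 2 × (1.96 + 0.8416)² × 58² / 23.4² = 96.4, so 97 per arm. Then 97 × 1.15 = 111.55, and 111.55 / 0.70 = 159.4, so 160.
- Final size: 380 × 0.75 / 1.15 = 247.8 effective per arm. This gives power of 92.4% for 65% v 50% and 83.8% for 65% v 52%, as claimed.

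**2. Design effect for the treatment comparison.** Only the intervention arm is clustered, so with equal arms and equal total variance the design effect (DE) is the average of 1 and 1 + (m − 1) × ICC.
- m = 7: 1 + 6 × 0.04 = 1.24, average 1.12.
- 380 × 0.75 = 285 evaluable over 30 clinicians, m = 9.5: 1 + 8.5 × 0.04 = 1.34, average 1.17.
- The plan's stated factor, 1.15, lies between these.

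**3. Effect of ignoring it.** The standard error is too small by 1 − 1/√DE. The true two-sided type I error is 2[1 − Φ(1.96/√DE)].

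| DE | SE too small by | True type I error | 95% CI coverage |
|---|---|---|---|
| 1.12 | 5.5% | 6.4% | 93.6% |
| 1.15 | 6.7% | 6.8% | 93.2% |
| 1.17 | 7.5% | 7.0% | 93.0% |

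**4. Simulation check.** An unadjusted comparison of means was simulated 10,000 times with no treatment effect, 285 per arm, 30 clinicians, three clinics, and arms balanced within clinic. With clinician ICC 0.04 the type I error was 6.9% to 7.2% across assumed clinic variances of 0, 2% and 5%. With no clinician effect and clinic variance of 5% or 2% (assumed), it was 4.4% or 4.7%. Omitting clinic alone therefore errs on the cautious side, as expected when allocation is stratified by clinic.

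**5. Power from covariates.** For a continuous outcome with 80% power unadjusted, power after adjustment is Φ[(1.96 + 0.8416)/√(1 − r²) − 1.96]. This gives 82% at r = 0.2, 84% at 0.3 and 90% at 0.5. The document gives no value of r, so these figures are illustrations only.

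**The case against.** The strongest reply is that silence is being read as exclusion. The article is condensed, a fuller analysis plan may exist, and the sentence ends with a qualifier that lets the baseline term drop where there is none. A reader might infer that these outcomes are adjusted solely for baseline value and that all else is deliberately left out. The text does not say so. The primary outcome is itself a Form 90 measure without a Form 90 baseline, and the plan handles it with baseline harmful drinking, so the same substitute may have been intended for its companions. This limits the point to what the sentence says. It does not remove it: the article states a method for this tier, and that method names no clustering term and no substitute covariate, while the sentence before it expressly carries the primary approach to one outcome.

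Three stronger readings are tempting and are not supported.

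- *Omitting clinic also overstates certainty.* Allocation is stratified by clinic, so the omission makes standard errors slightly too large. Only the clinician omission works the other way.
- *Type I error reaches 7.3%.* This comes from averaging 1 and 1 + 9.5 × 0.04/0.96, which gives a design effect of 1.198. A naive analysis already absorbs clinician variance in its variance estimate, so 1.17 and about 7.0% is the right figure for equal clusters of 9.5. With more than 30 clinicians the average cluster is smaller still.
- *Power is materially lost.* Eligibility requires heavy drinking occasions at least monthly, which narrows the range of the M-SASQ, so its correlation with outcome may be low. The power formula also does not cover the binary outcomes.

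It is also fair that the full mixed logistic model may fail for sparse events such as unwanted pregnancy. The fix has to allow for that.

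**Conclusion.** The point stands, at modest size. As stated, the model for the other secondary outcomes lacks the clinician and clinic terms and the age, sex and baseline-drinking covariates of the primary model. For the two Form 90 outcomes and the AUDIT-C outcome, the one named covariate does not exist. If the wording is followed, standard errors are about 5.5% to 7.5% too small and the nominal 5% test runs at about 6.4% to 7.0% (6.8% at the plan's own factor of 1.15). This rests on the plan's ICC of 0.04 applying to these outcomes, equal total variance in the arms, and roughly equal cluster sizes of 7 to 9.5.

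The missing baseline value concerns the three alcohol outcomes. Baseline sexual behavior is collected, so for those outcomes the issue is mainly the clustering terms. The primary and main secondary analyses are not affected.

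**What to change.** Replace the sentence on other secondary outcomes with wording such as:

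> Other secondary outcomes will be analysed by linear or logistic regression with the structure of the primary model: clinic, treating clinician in the intervention arm, age and sex. The baseline M-SASQ category will be the drinking covariate for the Form 90 and AUDIT-C outcomes, for which no baseline value is collected. Other outcomes will be adjusted for their own baseline value where it was collected. If the mixed model does not converge for a sparse binary outcome, a logistic model with fewer covariates and clinician-clustered robust standard errors will be used.

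The variables are already collected and the model structure is already being fitted, so the change is to wording only. The article reports recruitment as ongoing, so it could be made before analysis. The costs are slightly wider intervals once clinician clustering is counted, and some work on convergence for rare events. Adding a baseline Form 90 or AUDIT-C is not needed and would work against the deliberate choice to keep baseline alcohol assessment short.
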